#### Secondary endpoints

Acute toxicity of preoperative radio-immunotherapy followed by radical cystectomy until 3 months after end of therapy according to CTCAE v4. Typical, predefined side effects of surgery will be excluded from analysis.Rate of immune related toxicities: Immune mediated pneumonitis, colitis, hepatitis, hypophysitis, adrenal insufficiency, hypo−/hyperthyroidism, diabetes (type 1), nephritis, immune mediated skin reactionsLate toxicity during 1 year follow up according to CTCAE v4Disease free survival (DFS) defined by local recurrence or distant metastasis or death in R0 resected patients during 1 year follow up starting at the date of cystectomyTime to death by any cause during 1 year follow up (overall survival (OS)) starting at the date of cystectomyRadiological overall response rate after radio-immunotherapy before radical cystectomy (complete response, partial response, stable disease, progressive disease)ypT0 rate after radical cystectomySurgical margin status after cystectomy (R0/R1/R2)

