**Methods:**

**Study design: “**RACE IT” (AUO AB 65/18) is an investigator initiated, prospective, multicenter, open, single arm phase II trial sponsored by Technical University Munich. Study drug and funding are provided by the company Bristol-Myers Squibb.

**Study treatment:** Patients will receive Nivolumab 240 mg i.v. every 2 weeks for 4 cycles preoperatively with concomitant radiation therapy of bladder and pelvic region (max. 50.4 Gy). Radical cystectomy with standardized bilateral pelvic lymphadenectomy will be performed between week 11–15.

**Primary endpoint:** Rate of patients with completed treatment consisting of radio-immunotherapy and radical cystectomy at the end of week 15.

**Secondary endpoints:** Acute and late toxicity, therapy response and survival (1 year follow up).

**Main inclusion criteria:** Patients with histologically confirmed, locally advanced bladder cancer (cT3/4, cN0/N+), who are ineligible for neoadjuvant, cisplatin-based chemotherapy or who refuse neoadjuvant chemotherapy.

**Main exclusion criteria:** Patients with metastatic disease (lymph node metastasis outside pelvis or distant metastasis) or previous chemo-, immune- or radiation therapy.

**Planned sample size:** 33 patients, interim analysis after 11 patients.

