### Aims

The primary objective of RACE IT is to evaluate safety and feasibility of the combined application of preoperative radiation therapy with the PD-1 checkpoint-inhibitor Nivolumab followed by radical cystectomy in patients with locally advanced bladder cancer. We secondarily hypothesize that the combined application of preoperative radiation therapy with the PD-1 checkpoint-inhibitor Nivolumab before radical cystectomy leads to improved disease-free survival (DFS) and overall survival (OS) compared to historical controls.

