### Treatment and follow up

Treatment starts after successful completion of the screening phase and confirmation of eligibility. Nivolumab 240 mg flat dose will be given intravenously on day 1. Nivolumab will be given every 2 weeks for a total of 4 cycles. The last infusion will be in week 7. Standard radiation therapy will start on day 8 (week 2). The radiation therapy will be given in 28 fractions over approximately 5 and a half weeks. The total dose is 50.4 Gy in fractions of 1.8 Gy per day with 45 Gy of the pelvic region and a consecutive boost of bladder/tumor with 5.4 Gy. Imaging will be performed before start of treatment as baseline and repeated after finishing of study treatment before radical cystectomy to rule out progression or systemic disease. In case of systemic disease, no cystectomy will be performed in curative intention. The surgery consisting of open radical cystectomy with urinary diversion (ileum conduit or neobladder) and standardized pelvic lymphadenectomy will be performed within week 11–15. The standardized lymphadenectomy is exactly defined in a SOP and includes the external and internal iliac region, obturator fossa as well as commune iliac region.

Follow up for secondary endpoints will be starting at the date of cystectomy for 1 year (52 weeks). A schematic outline of the treatment plan is shown in Fig. 1.

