## Discussion

RACE IT study aims to evaluate immunotherapy with the PD-1 checkpoint-inhibitor Nivolumab combined with radiation therapy followed by radical cystectomy for patients with locally advanced bladder cancer.

Survival rates of patients with locally advanced bladder cancer treated with radical cystectomy are poor. The addition of neoadjuvant chemotherapy could increase 5-year survival only about 5–8% [2, 6] indicating the need for novel additional therapies. Retrospective analyses have shown promising results for the use of RCHT in the neoadjuvant setting, with 5-year disease specific survival (DSS) of 62% compared to 27% in their historical “cystectomy only” cohort [17]. Around 50% of patients are ineligible to receive neoadjuvant chemotherapy mainly because of impaired renal function [4], thus ongoing trials evaluate the benefit of immune-checkpoint inhibitors in a neoadjuvant setting since they can be given regardless of kidney function. An Open-Label, Single-Arm, Phase II Study (PURE-01) analyzed the activity of pembrolizumab as neoadjuvant immunotherapy before radical cystectomy for MIBC and showed downstaging to pT < 2 in 54% of patients and 42% pT0-patients in RC after 3 cycles of pembrolizumab. Notably, all 55 patients enrolled in the study underwent radical cystectomy [22]. Three patients (6%) had grade 3 AEs (diarrhea, hyperkaliemia, ALT/AST-increase) that caused pembrolizumab discontinuation for one patient. Response rates were significantly dependent on the PD-L1 status (highly enriched in patients with PD-L1 CPS ≥ 10% vs. no appreciable antitumor effects patients with CPS < 10%) and significant association between tumor mutation burden (TMB) and pT0 was observed. Interim results of the ABACUS-trial showed that neoadjuvant atezolizumab is safe and associated with a significantly improved pathological CR (29%). Treatment related grade 3/4 toxicity occurred in 12% of patients and 7 out of 69 patients (10%) did not have cystectomy [13].

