These studies show promising results with high rates of downstaging, but the responses were significantly dependent on the PD-L1 status [22]. Response rates might even be increased with concomitant radiation therapy, which leads to immunogenic cell death, release of T-cell attracting cytokines and upregulation of surface molecules. There is preliminary evidence to believe that the combination of radiation therapy with immunomodulating drugs has a promising potential for synergistic and off-target effects, without severe toxicities and might improve downstaging and operability of the tumor [18, 19]. We believe that response and survival rates might be improved due to the promising results of immunomodulating agents in MIBC and metastatic bladder cancer as well as the possible synergistic effects of radiation therapy and PD-1 inhibition.

One critical point of neoadjuvant therapy in general is the delay or even truncation of definitive therapy. This study holds a risk of delay of surgery and consecutive progression-risk for patients. In the PURE-01 trial the neoadjuvant administration of immunotherapy did not delay planned surgery [22]. Available data and clinical experience suggest, that the combination of radiation and immunotherapy is well tolerated and does not lead to excess toxicity [18].

The experience with preoperative RCHT in the setting of trimodal therapy shows reasonable anti-tumor activity [17]. Therefore, we assume that our planned treatment will at least contribute to inhibition of tumor progression. And due to the poor prognosis of this patient population, we would accept the risk of a delay compared to immediate cystectomy or neoadjuvant chemotherapy, given the expected benefit.

In concern of organ specific toxicities, especially gastrointestinal toxicity is a potential risk for patients, which cannot be quantified due to the lack of high quality data in the setting of combined radioimmunotherapy.

Follow-up is limited to 1 year after cystectomy, but we have to emphasis that in this trial the DFS and OS are secondary objectives. Due to the fact, that most recurrence occur in the first year after surgery, the one-year DFS and OS rates as secondary endpoints will provide sufficient data of treatment efficacy in order to plan a consecutive phase III trial.

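### DFS and OS start at cystectomy, and DFS is limited to R0 resections, so pre-operative failures cannot lower the survival rates meant for the historical comparison and phase III planning

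*Protocol article*

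**What the plan says.** All references are to the protocol article.

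- **Secondary endpoints.** DFS counts local recurrence, distant metastasis or "death in R0 resected patients during 1 year follow up starting at the date of" cystectomy. OS is time to death from any cause over one year, with the same start date.
- **Treatment and follow up.** "Follow up for secondary endpoints will be starting at the date of cystectomy for 1 year (52 weeks"). Nivolumab starts on day 1 and radiotherapy on day 8. According to the Abstract, "Radical cystectomy with standardized bilateral pelvic lymphadenectomy will be performed between week 11–15". After imaging repeated before surgery, "In case of systemic disease, no cystectomy will be performed in curative intention".
- **Table 2.** Survival status is scheduled only at visits 7 to 10, all of them timed from the operation.
- **Aims.** The secondary hypothesis is that the regimen "leads to improved disease-free survival (DFS) and overall survival (OS) compared to historical controls".
- **Discussion.** "This study holds a risk of delay of surgery and consecutive progression-risk for patients". The section also states that "the one-year DFS and OS rates as secondary endpoints will provide sufficient data of treatment efficacy" for planning a phase III trial.
- **Where pre-operative failure is counted.** The primary endpoint is completion of radio-immunotherapy and cystectomy by the end of week 15, analysed on the Full Analysis Set. Progressive disease is a category of the pre-operative radiological response. Margin status (R0/R1/R2) is a secondary endpoint of its own.

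**The concern.** The treatment under study is the preoperative radio-immunotherapy, but the survival clocks start only once it is over and the patient has reached surgery. A patient who dies before surgery or is never operated on has no start date for either endpoint. A patient with an R1 or R2 resection has no DFS. Entry to the analysis thus depends on how well the regimen worked and was tolerated.

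This would matter little for a purely descriptive account of the course after surgery. The article asks more of these rates: they carry the hypothesis of improvement over historical controls and are called sufficient efficacy data for a phase III trial. Patients in a series taken straight to cystectomy did not first have to get through 11–15 weeks of treatment and a restaging scan. The harm that the Discussion itself names, progression while surgery waits, can lower neither the reported DFS nor the reported OS.

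**Working it through.** **The plan's own figure.** No rate, power or control value is stated for DFS or OS. The only design figure is for the primary endpoint: 30 patients, 70% against 92.5%, two-sided 5%, 82% power. It reproduces. With an exact binomial test and an upper tail of at most 2.5%, the rule is at least 27 completers of 30; the tail probability at 70% is 0.0093 and the power at 92.5% is 0.8155. This concern does not touch that test. The rule does show that the trial can succeed with 3 of 30 patients (10%) not completing.

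**Inputs from the document.**

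- Non-cystectomy rates in the two neoadjuvant trials cited in the Discussion: 0 of 55 (pembrolizumab), and for atezolizumab "7 out of 69 patients (10%) did not have cystectomy", 7/69 = 10.1%. Together 7/124 = 5.6%, or 33 × 0.056 = 1.9 patients of 33.
- Planned completion rate: 92.5%. It stands in for the cystectomy rate here. The two are not identical, because a patient operated after week 15 is a non-completer but still has a cystectomy date.

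**Assumptions (no such figures in the document).** R0 share among operated patients 90–100%; one-year DFS in R0 patients 70%; one-year OS in operated patients 90%; survival of unoperated patients at the landmark 0–50%.

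**Landmark one year after surgery.** With non-resection and R1/R2 counted as failures:

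all-treated event-free share = P(cystectomy) × P(R0) × DFS in R0 patients

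| P(cystectomy) | P(R0) | Patients in DFS set, of 33 | DFS as defined | All-treated share |
|---|---|---|---|---|
| 100% (55/55) | 100% | 33.0 | 70% | 70.0% |
| 100% (55/55) | 90% | 29.7 | 70% | 63.0% |
| 92.5% | 100% | 30.5 | 70% | 64.7% |
| 92.5% | 90% | 27.5 | 70% | 58.3% |
| 89.9% (62/69) | 90% | 26.7 | 70% | 56.6% |

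For example, 0.925 × 0.90 × 0.70 = 0.583.

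all-treated OS = P(cystectomy) × S(operated) + [1 − P(cystectomy)] × S(unoperated)

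At 92.5% operated: 0.925 × 0.90 + 0.075 × 0 = 83.3%, up to 0.925 × 0.90 + 0.075 × 0.5 = 87.0%, against 90% as defined. The gap is 3 to 7 points.

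**Landmark one year after first dose.** Weeks 11 and 15 begin 10 and 14 weeks after the first dose, which leaves 42 and 38 weeks after surgery. Assume a constant hazard after surgery.

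- DFS in R0 patients: 0.70^(42/52) = 0.750 and 0.70^(38/52) = 0.771. All treated, at 92.5% operated and 90% R0: 0.925 × 0.90 × 0.750 = 62.4% and 0.925 × 0.90 × 0.771 = 64.2%. The gap to 70% is about 6 to 8 points.
- At 92.5% operated and 100% R0, the same step gives 0.925 × 0.750 = 69.4% and 0.925 × 0.771 = 71.3%, so the gap closes.
- OS in operated patients: 0.90^(42/52) = 0.918 and 0.90^(38/52) = 0.926. All treated: from 0.925 × 0.918 + 0 = 85.0% to 0.925 × 0.926 + 0.075 × 0.5 = 89.4%. The gap to 90% is about 1 to 5 points.

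The first-dose landmark gives smaller gaps because it removes up to 14 weeks of post-operative risk while it adds the pre-operative failures.

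**The case against.** The strongest replies, and what stands of each:

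- **Pre-operative failure is not hidden.** Non-resection by week 15 fails the primary endpoint, pre-operative progression appears in radiological response, and margins are reported. This stands. A reader might infer that such events never count in the trial; the document does not support that. They are missing only from DFS and OS, and reporting them elsewhere does not correct those two rates.
- **The number lost may be very small.** All 55 patients in the cited pembrolizumab trial were operated on. This stands, and any range has to start at zero. If every patient is operated on, OS loses no one, and DFS loses only R1/R2 resections.
- **Efficacy need not be overstated.** A reader might infer an overstatement of fixed size for both endpoints. With a first-dose origin two effects oppose each other, and for OS the net difference may be close to zero. This stands.
- **Historical figures are timed from surgery.** The five-year figure for node-positive disease in the Background is. A first-dose origin therefore brings a mismatch of its own. That is a reason to keep the surgery-timed measures, but matching the start date does not remove selection on a post-treatment outcome.
- **DFS in R0 patients is coherent.** Residual tumour is not disease-free. True; the difficulty lies in using it as the regimen's efficacy result.
- **OS is not limited to patients clear at restaging.** The text rules out surgery with curative intent only, so a patient with systemic disease who was operated on for another purpose would have an OS time. This stands.
- **The article is condensed, and Table 2 lists minimum assessments.** The full protocol may provide follow-up of unoperated patients. That would solve data collection, but not the endpoint definitions, which are explicit.

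**Conclusion.** The concern holds for DFS and OS as defined, and only for them. Pre-operative death, progression that precludes surgery and non-resection cannot lower either rate, and R1/R2 resection cannot lower DFS. Yet these rates are to support a comparison with historical controls and the planning of a phase III trial.

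At a fixed landmark after surgery the direction for DFS is certain: the all-treated event-free share is lower whenever any patient is not R0-resected. For OS it also requires that unoperated patients survive less well, which is plausible because they include pre-operative deaths and patients with systemic disease. The size cannot be derived from the document. The example of 58% instead of 70% rests on the planned 92.5% completion rate and on assumed values of 90% R0 and 70% DFS. With a one-year landmark from first dose the DFS gap is about 6 to 8 points under the same inputs, and the OS gap may be near zero.

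This should be fixed, but it does not invalidate the trial. DFS and OS are descriptive secondary endpoints without a test or threshold, and the success criterion rests on the primary endpoint alone.

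**What to change.** - Add OS from the first Nivolumab dose in all treated patients.
- Add event-free survival from the first dose in all treated patients. Count as events: progression that precludes curative cystectomy, no resection or R1/R2 resection, local recurrence, distant metastasis and death.
- Base the efficacy statements in the Aims and Discussion on these two measures.
- Collect survival status in unoperated patients to the same horizon.
- Keep surgery-timed OS and DFS in R0 patients as supportive descriptive analyses, for comparison with surgery-timed series. Report beside them how many treated patients each one leaves out, and why.

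**Cost.** Endpoint wording and a few extra survival contacts; dose dates, restaging results and margin status are already recorded. The event-free rate will probably look less favourable than the current DFS, and the new time origin differs from that of surgery-timed historical series. The survival contacts need to be arranged while patients are still in follow-up, since status that is not collected may not be recoverable at analysis.

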### Treatment and follow up

Treatment starts after successful completion of the screening phase and confirmation of eligibility. Nivolumab 240 mg flat dose will be given intravenously on day 1. Nivolumab will be given every 2 weeks for a total of 4 cycles. The last infusion will be in week 7. Standard radiation therapy will start on day 8 (week 2). The radiation therapy will be given in 28 fractions over approximately 5 and a half weeks. The total dose is 50.4 Gy in fractions of 1.8 Gy per day with 45 Gy of the pelvic region and a consecutive boost of bladder/tumor with 5.4 Gy. Imaging will be performed before start of treatment as baseline and repeated after finishing of study treatment before radical cystectomy to rule out progression or systemic disease. In case of systemic disease, no cystectomy will be performed in curative intention. The surgery consisting of open radical cystectomy with urinary diversion (ileum conduit or neobladder) and standardized pelvic lymphadenectomy will be performed within week 11–15. The standardized lymphadenectomy is exactly defined in a SOP and includes the external and internal iliac region, obturator fossa as well as commune iliac region.

Follow up for secondary endpoints will be starting at the date of cystectomy for 1 year (52 weeks). A schematic outline of the treatment plan is shown in Fig. 1.

**Fig. 1 Fig1:**
[figure not shown]
Schematic outline of the treatment plan. Patients with locally advanced bladder cancer, included in RACE IT study, will receive Nivolumab 240 mg i.v. every 2 weeks for 4 cycles preoperatively with concomitant radiation therapy of bladder and pelvic region (max. 50.4 Gy) Radical cystectomy with standardized bilateral pelvic lymphadenectomy will be performed between week 11–15. Follow up for secondary endpoints will be starting at the date of cystectomy for 1 year every 6 months

Basis of the follow up is the German bladder cancer guideline. Post-surgery visits at 6 and 12 weeks and 6 and 12 months after date of cystectomy include survival status, urine dipstick test, laboratory tests as well assessment of cystectomy histology and details of surgery (week 6 postop), assessment of subsequent therapy after surgery, symptoms, Adverse Event (AE), concomitant medication, ECOG score, ultrasound of both kidneys and a symptom oriented physical examination. A CT-scan of thorax, abdomen and pelvis with i.v. contrast will be performed at month 6 and 12. MRT of abdomen/pelvis with native CT thorax can be used in case of impaired kidney function or contrast medium allergies. The quality of life will be assessed at the screening-visit, pre-surgery and 3, 6 and 12 months after surgery with questionnaires (EORTC QoL-C30, ICIQ-SF, IIEF-5/6 (male) und FSFI-19 (female), FACT-Bl). A detailed flowchart for minimum assessments during treatment and follow up phase is shown in Table 2.

**Table 2 Tab2:** Flowchart for minimum assessments of treatment and follow up phase

	Study Phase	Screening	Treatment visit	Treatment visit	Treatment visit	Treatment visit	Treatment visit		Postop visit	Postop visit	Follow up visit	Follow up visit
	Therapy		Nivolumab cycle 1	Nivolumab cycle 2	Nivolumab cycle 3	Nivolumab cycle 4	End RIT/PreOP		Postop 6w	Postop 12w	Follow up 6 m postop	Follow up 12 m postop
	Timepoint	-d28 – d0	d1 (w1d1)	d15 (w3d1)	d29 (w5d1)	d43 (w7d1)	d64 (w10d1)		w17–21	w23–27	w37–41	w63–67
Procedures	Visit No	1	2	3	4	5	6		7	8	9	10
Informed Consent		X						Radical Cystectomy week 11–15				
Inclusion/Exclusion Criteria		X										
Medical History		X										
Prior cancer therapy		X										
ECOG/Performance Status		X	X	X	X	X	X		X	X	X	X
Physical Examination		X	X	X	X	X	X		X	X	X	X
Vital Signs		X	X	X	X	X	X		X	X		
Height/Weight		X	X	X	X	X	X		X	X		
Symptom/Adverse Event Assessment		X	X	X	X	X	X		X	X	X	X
Bladder/surgery specific AEs		X	X	X	X	X	X		X	X	X	X
Concomitant Medication		X	X	X	X	X	X		X	X		
Laboratory tests		X	X	X	X	X	X		X	X	X	X
HIV/Hepatitis test		X							X			
Pregnancy test (Serum)		X					X					
Urine analysis		X					X		X	X	X	X
Kidney Ultrasound		X							X	X	X	X
Imaging (CT/MRT)		X					X				X	X
Histology assessment		X							X			
QoL-Questionnaires		X					X			X	X	X
Exploratory biomarker blood draw		X					X			X		
Survival status									X	X	X	X
Review of subsequent therapy									X	X	X	X

### Adverse events

Adverse Events (AEs) will be collected during the complete study period (treatment and follow up). All severe adverse events (SAEs) will be collected starting with the screening period until visit 8 (12 weeks after surgery). AEs of interest are immune-mediated, which are specific events that include pneumonitis, diarrhea/colitis, hepatitis, nephritis/renal dysfunction, rash, and endocrine events (adrenal insufficiency, hypothyroidism/thyroiditis, hyperthyroidism, diabetes mellitus, and hypophysitis) for which subjects received immunosuppressive medication for treatment of the event, with the exception of endocrine events, which are included regardless of treatment since these events are often managed without immunosuppression.

In addition to the assessment of all AEs by CTCAE, surgery- and bladder related adverse events are explicitly asked for and collected in detail, including peri-operative and postoperative complications (such as revision surgery, transfusion, anastomotic stricture or insufficiency, ileus, sepsis, cardiovascular events and so on). The following typical, predefined side effects of surgery will be excluded from analysis: short term paralytic ileus post-surgery without need for intervention, short term reactive diarrhea post-surgery, short term and asymptomatic hydronephrosis without creatinine elevation post-surgery, bacterial colonization of indwelling catheters post-surgery.

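### The acute toxicity endpoint excludes short-lived post-operative diarrhoea with no grade, duration or intervention limit, so the acute gastrointestinal rate can be too low, and never too high, by an unknown amount

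*Protocol article*

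**What the plan says.** **Endpoint and window.** The article's Secondary endpoints section defines the endpoint as "Acute toxicity of preoperative radio-immunotherapy followed by radical cystectomy until 3 months after end of therapy according to CTCAE v4". It follows this with the rule "Typical, predefined side effects of surgery will be excluded from analysis".

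**The excluded effects.** The Adverse events section lists four, all post-operative: "short term paralytic ileus post-surgery without need for intervention, short term reactive diarrhea post-surgery", then transient hydronephrosis (no symptoms, no rise in creatinine), and bacterial colonisation of catheters.

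**Events of interest.** The same section describes immune-mediated events of interest as "specific events that include pneumonitis, diarrhea/colitis, hepatitis" and others. Apart from endocrine events, these count only where they are events "for which subjects received immunosuppressive medication for treatment of the event".

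**Collection.** Adverse events are recorded throughout treatment and follow-up, and "surgery- and bladder related adverse events are explicitly asked for and collected in detail". The rule therefore acts on the analysis, not on the data collected.

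**The stated unknown.** On organ-specific toxicity, the Discussion says that "especially gastrointestinal toxicity is a potential risk for patients, which cannot be quantified", for lack of good data on combined radio-immunotherapy.

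**The concern.** Post-operative diarrhoea in this trial has at least three possible sources: the operation, pelvic irradiation and PD-1 blockade. The exclusion depends on telling the first from the other two. The words that do this work are *short term* and *reactive*, and the article defines neither. There is no surgery-only group to show the background rate, and attribution is made by investigators who know the treatment.

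Safety is part of the primary objective under Aims, and the results are meant to inform a possible phase III trial. A rule that can take bowel events out of the acute toxicity rate, and can never add any, weakens that rate for the organ system about which the article says least is known.

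**Working it through.** **1. The plan's own figures.** The article gives no rate for gastrointestinal toxicity or for the excluded effects, so there is none to reproduce. Its one design calculation concerns the primary endpoint: n = 30, null rate 0.70, expected rate 0.925, two-sided 5%, power 82%. With an exact binomial and 0.025 in the upper tail:
- P(X ≥ 26 | 0.70) = 0.0302, above 0.025;
- P(X ≥ 27 | 0.70) = 0.0093, so success needs 27 of 30;
- P(X ≥ 27 | 0.925) = 0.8155, which agrees with the stated 82%.

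This endpoint counts completed radio-immunotherapy and cystectomy by week 15. A diarrhoea episode after the operation cannot change it.

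**2. The four exclusions side by side.**

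| Excluded effect (all post-operative) | Limit other than *short term* |
|---|---|
| Paralytic ileus | no intervention needed |
| Diarrhoea | none; only the word *reactive* |
| Hydronephrosis | no symptoms, no creatinine rise |
| Catheter colonisation | none stated, but colonisation only |

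As worded, diarrhoea of any CTCAE grade can be excluded once it is called short term and reactive.

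**3. Can a treatment-related case fall there?** Under Treatment and follow up, the last nivolumab infusion is in week 7. Radiation starts on day 8 and lasts about 5.5 weeks, so it also ends in about week 7. Surgery in weeks 11–15 is then 11 − 7 = 4 to 15 − 7 = 8 weeks later. The acute window extends beyond surgery, so the plan itself treats this period as one in which toxicity of the whole sequence is to be counted.

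Take a diarrhoea episode soon after surgery that is caused by radiation or nivolumab, labelled reactive, and not treated with immunosuppression:
- acute toxicity: excluded by the rule;
- event of interest: not met, because no immunosuppression was given;
- rate of immune-related toxicities: this endpoint lists immune-mediated colitis, and a case labelled reactive has not been classed as that;
- late toxicity: listed without the exclusion sentence, but the Adverse events section states the exclusion without tying it to one endpoint, so this cannot be relied on.

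**4. Size.** If k of n patients have a gastrointestinal event, and m of them have no counted event other than an excluded one, the reported rate is (k − m)/n instead of k/n. The change is −m/n, which is never positive.
- n = 33: 1/33 = 3.0 points per patient.
- n = 30: 1/30 = 3.3 points per patient.
- A patient with another counted event in the same category, such as diarrhoea during radiation, adds 0.

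Illustration with an assumed k = 9 of n = 30 and exact 90% intervals:

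| m | Reported rate | 90% CI |
|---|---|---|
| 0 | 9/30 = 30.0% | 16.6–46.5 |
| 1 | 8/30 = 26.7% | 14.0–43.0 |
| 2 | 7/30 = 23.3% | 11.5–39.4 |
| 3 | 6/30 = 20.0% | 9.1–35.7 |
| 4 | 5/30 = 16.7% | 6.8–31.9 |

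Both k and m are assumptions. The article supplies neither, and m may be zero.

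**The case against.** The case for the exclusion is a serious one. It is predefined. In a single-arm trial, counting routine effects of cystectomy would make the combination look more toxic than it is, so setting them apart is legitimate. Which version is called main is partly preference. The article also condenses a full protocol that may define the terms, and it does not say that the excluded events will go unlisted. All of this stands. It does not cure a rule that, as published, drops diarrhoea whatever its grade while bounding ileus and hydronephrosis.

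Stronger readings are tempting, but the documents do not support them:
- *The safety result is biased downward.* Bias needs treatment-related events to be labelled as surgical. The article makes that possible but does not show that it happens.
- *The rule removes the bowel toxicity of radiation plus nivolumab.* All four exclusions are post-operative. Events at the nivolumab visits and at the week-10 visit before surgery remain, as does colitis treated with immunosuppression.
- *Ileus is removed.* Only short-lived ileus needing no intervention is, and ileus is named among the surgical complications recorded in detail.
- *Many points are lost.* Assuming that 10–30% of patients have such events would give 3 to 10 of 33, or 9.1 to 30.3 points. The article gives no such incidence, and the sum also requires that none of those patients had any other counted gastrointestinal event.

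**Conclusion.** The point holds for the diarrhoea item. The acute gastrointestinal toxicity rate, part of a secondary endpoint, can be understated and cannot be overstated by this rule. The amount is unknown: zero if no treatment-related case is labelled reactive, and at most 3.0 points (n = 33) or 3.3 points (n = 30) for each patient whose only counted event is removed.

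This rests on two assumptions: that the published wording is the operative rule, and that attribution after surgery is a matter of judgement with no stated criteria. The primary endpoint, its power and the success rule are untouched. The change is worth making because the affected organ system is the one the article singles out as unquantified, and because the data will already be in hand.

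**What to change.** Replace the blanket exclusion in Secondary endpoints and Adverse events with reporting both ways, for example:

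> Acute toxicity is tabulated by CTCAE grade for all events, and again without the four predefined surgical effects. Those effects are also shown in a row of their own.

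In addition, do not let the diarrhoea exclusion apply regardless of CTCAE grade. Define *short term* and *reactive* by duration and grade, with values chosen by the clinical team before the analysis. If the full protocol already contains such limits, cite them; reporting both ways is still needed.

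Cost: one extra table row, with no new data collection and no change to the sample size or the primary test. The rate that includes all events will be somewhat higher and will contain surgical background, which is why the two rates should be shown together.
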